### The First Phase

In the first phase, pregnant women attending prenatal care centers of urban areas of Masjed-Soleyman and Shushtar were recruited from July 1-September 31, 2014. Due to the blinding purposes and to avoid contacts among study subjects [34], we chose 2 cities with similar cultural, geographic, nutritional habits, and sun exposure conditions; one of these cities was assigned to intervention.

Masjed-Soleyman County is in the northeast of Khuzestan province. Its area is 9/6327 km^2^ with a population of 103,369 people with Persian ethnicity. This is a sunny region with a hot and humid climate. Its altitude is 260 meters above sea level. In terms of geographical location, it is between 31°59′ E longitude and 49°17′ N latitude. Shushtar County is in the north of Khuzestan. Its area is 2436 km^2^ with a population of 192,361 people with Persian ethnicity. The climate is similar to Masjed-Soleyman. Its altitude is 150 meters above sea level. In terms of geographical location, it is between 48°20′ E longitude and 32°30′ N latitude.

### Blood Assessments

Upon enrollment into the study, a fasting blood sample was obtained from all participants. Separated serum samples by centrifugation were transferred to the central laboratory of Masjed-Soleyman (cold chain was kept during storage and transfer processes). The serum samples of participants in Shushtar were stored and kept frozen at -80°C until assayed at the end of the study, but at that time the serum concentration of vitamin D of Masjed-Soleyman participants were promptly measured. Based on 25(OH)D levels, mothers were divided as severe deficient (<10ng/ml), moderate deficient (10-20ng/ml), and normal status (>20ng/ml) [1]. The scale to express 25(OH)D status results was according to ng/ml; each 1 ng/ml is equal to 2.496 nmol/L.

Those participants from Shushtar and those with serum vitamin D>20 ng/ml from Masjed-Soleyman served as controls and were followed until delivery. Subjects with severe and moderate vitamin D deficiency from Masjed-Soleyman were selected for the second phase of the study and were randomly allocated to one of the treatment modalities presented in Figure 1.

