**Methods:**

This was a two-phase study. First, a population-based cross-sectional study was conducted; recruiting 1600 and 900 first trimester pregnant women from health centers of Masjed-Soleyman and Shushtar, respectively, using stratified multistage cluster sampling with probability proportional to size (PPS) method. Second, to assess the effect of screening strategy on maternal and neonatal outcomes, Masjed-Soleyman participants were assigned to a screening program versus Shushtar participants who became the nonscreening arm. Within the framework of the screening regimen, an 8-arm blind randomized clinical trial was undertaken to compare the effects of various treatment protocols. A total of 800 pregnant women with vitamin D deficiency were selected using simple random sampling from the 1600 individuals of Masjed-Soleyman as interventional groups. Serum concentrations of 25(OH)D were classified as: (1) severe deficient (<10ng/ml), (2) moderate deficient (10-20ng/ml), and (3) normal status (>20ng/ml). Those with severe and moderate deficiency were randomly divided into 4 subgroups and received vitamin D3 based on protocol and were followed until delivery. Data was analyzed according to the intention-to-treat principle.

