## Methods

### Overall Study Design

This was a 2-phase population-based study. The first phase comprised a population-based cross-sectional study in which 1600 and 900 first trimester pregnant women attending health centers of Masjed-Soleyman and Shushtar, Khuzestan province, Iran were recruited using stratified multistage cluster sampling with probability proportional to size (PPS) method [33]. In the second phase of this study, within the framework of screening regimen, Masjed-Soleyman participants with vitamin D deficiency were assigned to a screening program versus Shushtar participants (as nonscreening arm) to assess the effectiveness of various treatment regimens. Pregnancy outcomes including preterm delivery, miscarriage, preeclampsia, gestational diabetes, and type of delivery and neonatal outcomes including birth weight (gr), head circumference (cm), height (cm), APGAR score 1, 5 minute, icterus, cord falling off time (day), serum calcium (mg/dl) level, and cord concentration of 25(OH)D (ng/ml) were recorded.

Shushtar participants (as nonscreening arm) served as controls and were followed till delivery and any adverse pregnancy outcomes were assessed.

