### The Second Phase

In the second phase of the study, to assess the effect of screening strategy on maternal and neonatal outcomes, Masjed-Soleyman participants were assigned to a screening program versus Shushtar participants acting as the nonscreening arm. Within the framework of the screening regimen, an 8-arm blind randomized clinical trial was undertaken to compare the effects of various treatment protocols. Due to the cost and complexity of the process, 800 pregnant women with vitamin D deficiency from Masjed-Soleyman were randomly allocated to 1 of the designed intervention programs according to the study Figure 1. The remaining women with vitamin D deficiency were referred to specialists for further treatments. Participants of Shushtar did not receive any vitamin D supplementation. However, the comparison of the basic confounders between the initial recruited sample in Masjed-Solayman and the women allocated to intervention indicated no statistically significant difference and hence no selection bias occurred during the allocation of treatment (Table 4).

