#### Women With Normal Status (Group C)

Subjects in this group and the pregnant women recruited from Shushtar city comprised our controls. They had access to standard prenatal care and were followed until delivery. In the case of any adverse outcome, it was managed according to the perinatal guidelines. Blood sampling from subjects in this group and those from Shushtar was obtained at the first visit. Similar to others groups, another sample was obtained from mothers and umbilical cord at the time of delivery.

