**Occupation**										
	Worker	14	1.60	21	2.30	35	1.90	.46
	Clerk	135	15.00	119	13.20	254	14.10	
	Self-employed	111	12.30	117	13.00	228	12.70	
	Housewife	640	71.10	643	71.40	1283	71.30	
	Total	900	100.00	900	100.00	1800	100.00	

^a^The chi-square statistic is significant at the .05 level.

^b^Fisher exact test results is significant at the .05 level.

For the second phase of the study, as statistically was calculated, we needed 800 women, therefore the remaining women were referred to a specialist for further treatments. However, in terms of baseline features except for vitamin D levels, there was no significant difference between the initial sample in Masjed-Soleyman and those who were allocated to intervention (Table 4). The difference for vitamin D is ignorable though.

**Table 4 table4:** Comparison of baseline characteristics between the initial sample of Masjed-Soleyman participants and those allocated to intervention.

Baseline variables	Initial sample (n=1581)	Allocated for intervention (n=900)	*P* value^a^
Age (year)	29 (25-32)^b^	29 (25-32)	.77
First pregnancy age (year)	20 (18-22)	20 (18-22)	.94
First delivery age (year)	20 (18-22)	20 (18-22)	.73
Gestational age (week)	10 (9-12)	10 (9-12)	.97
Vitamin D	11.9 (8-17)	11.2 (7-16)	.01
Number of children	^b^1 (0-2)	1 (0-2)	.67
Gravity	2 (1-3)	2 (1-3)	.62
Parity	1 (0-2)	1 (0-2)	.47
Number of abortions	0 (0-0)	0 (0-0)	.94

^a^*P* value obtained from nonparametric Mann-Whitney test for nonnormal variables.

^b^Median (interquartile range, Q1-Q3).

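### The protocol gives conflicting definitions of the screened arm and of the role of screened women with normal vitamin D; two of the readings would confound the screening comparison with baseline 25(OH)D

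*Protocol article*

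**What the plan says.** The protocol article describes the two-city groups in several places.

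- **Abstract, Methods:** "Masjed-Soleyman participants were assigned to a screening program versus Shushtar participants who became the nonscreening arm". There is no restriction to deficient women.
- **The Second Phase:** "Masjed-Soleyman participants were assigned to a screening program versus Shushtar participants acting as the nonscreening arm". Again there is no restriction.
- **Overall Study Design:** "Masjed-Soleyman participants with vitamin D deficiency were assigned to a screening program versus Shushtar participants (as nonscreening arm". Here the screened side is deficient women only. The same section adds "Shushtar participants (as nonscreening arm) served as controls and were followed till delivery".
- **Blood Assessments:** "Those participants from Shushtar and those with serum vitamin D>20 ng/ml from Masjed-Soleyman served as controls and were followed until delivery".
- **Women With Normal Status (Group C):** "Subjects in this group and the pregnant women recruited from Shushtar city comprised our controls".
- **The Second Phase, on deficient women beyond the 800 randomised:** "The remaining women with vitamin D deficiency were referred to specialists for further treatments".
- **Results, Table 4:** an initial sample of 1581 beside a column headed "Allocated for intervention (n=900"). The text gives 800 allocated. Table 2 also compares 900 Masjed-Soleyman women with 900 Shushtar women.

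The Statistical Analysis section does not say which women form the groups of the screening comparison.

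**The concern.** A screening strategy acts on everyone who is screened. Women who screen normal belong to it, as do deficient women who were found by screening and referred elsewhere. If the screened arm holds only deficient women while Shushtar is unselected, the arms differ in baseline 25(OH)D because of how they were chosen. If the normal-status women also move to the control side, the gap widens.

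The supplementation question has the same difficulty: treated deficient women are not comparable with controls that include sufficient women.

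Research questions 3 and 5 (does supplementation help, and is universal screening reasonable) rest on these contrasts. As written, two analysts could follow different sections of the article and reach different estimates.

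**Working it through.** **1. Readings that the text allows**

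| Reading | Screened side | Comparison side | Source |
|---|---|---|---|
| A | deficient Masjed-Soleyman | Shushtar plus normal-status Masjed-Soleyman | Overall Study Design combined with Blood Assessments and Group C |
| B | deficient Masjed-Soleyman | Shushtar | Overall Study Design |
| C | all Masjed-Soleyman | Shushtar | Abstract; The Second Phase |

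The article gives no figure for the size of this problem, so there is none to reproduce.

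**2. Share with normal status**

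Input: baseline 25(OH)D in the initial Masjed-Soleyman sample, 11.9 (8-17), n=1581 (Table 4). A log-normal shape is assumed.

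- σ = ln(17/8)/1.349 = 0.559
- P(>20) = 1 − Φ[ln(20/11.9)/0.559] = 0.176
- Normal status: 0.176 × 1581 ≈ 279
- Deficient: 1581 − 279 = 1302
- Deficient but not among the 800: about 502

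**3. Risk ratio when nothing works**

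Assumptions: identical cities, no effect of screening or treatment, risk 1 (relative) in sufficient women and k in deficient women.

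- Shushtar risk: S = 0.176 + 0.824k
- Pooled control risk: (900 × S + 279 × 1)/1179
- Reading A: k/pooled. Reading B: k/S. Reading C: S/S.

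| k | S | Pooled | RR, A | RR, B | RR, C |
|---|---|---|---|---|---|
| 1.0 | 1.000 | 1.000 | 1.00 | 1.00 | 1.00 |
| 1.5 | 1.412 | 1.314 | 1.14 | 1.06 | 1.00 |
| 2.0 | 1.824 | 1.629 | 1.23 | 1.10 | 1.00 |

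With an assumed 8% risk in sufficient women and 800 women on the screened side, the chance of a false two-sided 5% result is about 18% (k=1.5) to 45% (k=2) under A, and about 7% to 13% under B.

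**4. Effect on a real benefit**

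Suppose treatment cuts risk in deficient women by 20%.

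- A: 0.80 × 1.14 = 0.91, up to 0.80 × 1.23 = 0.98
- B: 0.80 × 1.06 = 0.85, up to 0.80 × 1.10 = 0.88
- C, all deficient women treated: (0.824 × 1.5 × 0.80 + 0.176)/1.412 = 0.82 for k=1.5, and also 0.82 for k=2. This is the true strategy effect, diluted only by women who need no treatment.

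**5. What the 900 look like**

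Table 2 gives 11 (7-16) in both cities, P=.96. Table 4 gives 11.2 (7-16) for its 900. From the log-normal fit:

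- deficient women only: about 10.5 (7.5-14.1)
- 800 deficient plus 100 normal-status women: about 11.3 (7.9-15.8)
- Shushtar pooled with the normal-status women: about 14 (8-23)

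The reported 900 fit a group that includes some normal-status women, and the Shushtar column fits Shushtar alone. The article does not state how the 900 were formed.

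**The case against.** A reader might infer that the screening comparison is biased by construction, with normal-status women pooled into the non-screening arm. The documents do not support that. Wherever the non-screening arm is named, it is Shushtar alone. Where Group C women are called controls, the word is attached to follow-up until delivery under standard care, and it may mean only an untreated reference group. No section states a pooled comparator. Table 2, with the same vitamin D distribution in both cities, does not look like deficient women against pooled controls. The deficient-only wording occurs in one sentence, which also mentions treatment regimens and may have merged the screening comparison with the eight-arm trial. All of this stands.

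A reader might also infer that the bias necessarily runs against screening. It does so only if deficiency raises risk. The Introduction calls the evidence inconclusive, and research question 2 asks whether such a relation exists.

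Nor is a breach of intention-to-treat shown: no screening analysis set is defined that could be breached. Referral to specialists is not a statement that those women leave the analysis, and the Abstract says the 800 were drawn by simple random sampling.

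Figure 1 is not available here, and analysis sets are often left to a fuller document. That excuses missing detail. It does not excuse printed definitions that conflict, and the objection does not remove that conflict.

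**Conclusion.** The concern holds as an internal contradiction about who is in the screened arm and what role screened women with normal status play, made harder to resolve by the unexplained 900. It is not shown that the biased groupings were planned.

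The cost of following the wrong sentence is conditional. For an assumed 1.5- to 2-fold excess risk, the null risk ratio is about 1.06 to 1.10 without pooling and 1.14 to 1.23 with it. It is 1.00 for all-versus-all, and 1.00 under every reading if deficiency carries no excess risk. These figures also assume comparable cities and a log-normal 25(OH)D distribution.

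This should be settled before the two-city comparison is analysed, because the main question currently has no single defined population.

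**What to change.** Reconcile the Abstract, Overall Study Design, Blood Assessments, The Second Phase, the Group C section and Table 4, and define two contrasts.

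1. **Screening.** All enrolled Masjed-Soleyman women (normal, randomised and referred) versus all Shushtar women. Where outcomes of referred or normal-status women are unavailable, weight the followed women by the inverse of the selection fraction within vitamin D stratum (<10, 10-20, >20 ng/ml). Weighting matters: 800 deficient women plus all normal-status women, unweighted, would be 279/1079 = 26% normal instead of 17.6%.
2. **Supplementation.** Randomised deficient women versus Shushtar women whose stored baseline sample shows deficiency, within the same severity strata.

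Do not pool Group C with Shushtar in either contrast; report it as a separate reference group. Explain 800 versus 900, and show Tables 2 and 3 for the full Masjed-Soleyman sample against Shushtar.

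**Cost.** Mostly wording and regrouping. The stored Shushtar samples are already due for assay. Outcomes of referred women may have to be taken from records. Weighting widens intervals slightly. As an illustration, take 400 women per deficiency stratum (four arms of 100) and the log-normal shares (about 597 severe, 705 moderate). The weights are then 597/400 = 1.49 and 705/400 = 1.76, with 1 for the 279 normal. The effective sample is (Σw)²/Σw² ≈ 1036 of 1079, so standard errors rise by about 2%.

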### Subject Recruitment and Eligibility Criteria

Pregnant women, aged 18-40 years, were eligible if they had gestational age <14 weeks based on last menstrual period or obstetrical estimation, singleton pregnancy, and had planned to receive ongoing prenatal and delivery in the Masjed-Soleiman. Participants were excluded if they consumed multivitamins containing more than 400 international unit (IU) per day of vitamin D3; used anticonvulsants; and had history of chronic diseases like diabetes, hypertension, renal dysfunction, liver diseases, and complicated medical or obstetrical history.

### Data Collection and Quality Control Procedures

At first, midwives responsible for prenatal care in the selected health centers were invited to attend a workshop designed for explaining the study objectives and procedure. Thereafter, first trimester pregnant women seeking maternity care during their first routine prenatal visit were invited to participate in the study after providing a detailed explanation of the study procedure; they signed a written informed consent during recruitment covering all trial procedures and data collection. For gestational age calculation, the first day of the last menstrual cycle (LMP) for women with regular cycles and ultrasonography for those with irregular cycles or those who could not precisely recall their LMP was used. Pregnant women received prenatal care and each adverse pregnancy outcome was managed according to the standard guidelines. At enrollment, for each participant a questionnaire that included information on sociodemographic, anthropomorphic, behavioral, and reproductive characteristics was completed by a trained interviewer.

Weight was measured with minimum clothing to the nearest 100 grams. Height was measured with a tape measure in standing position with normal posture of shoulders. Body mass index was calculated by dividing weight (kg) on height (m^2^). Systolic and diastolic blood pressures (SBP and DBP) were measured twice in a sitting position with a standard mercury sphygmomanometer after a 15-min rest and the mean of the 2 measurements was considered as SBP or DBP.

A fasting blood sample (5cc) was taken by venipuncture from the antecubital vein. Plasma was then separated by centrifugation (1500g, 10 min, 4˚C) in the central laboratory of Masjed-Soleyman and stored at −20˚C until analysis at the end of the week. Serum concentrations of 25(OH)D for the participants of Masjed-Soleyman were measured immediately, and subsequently their vitamin D status was determined (Table 1). The samples in Shushtar laboratory were stored at −80˚C until the end of the study; finally their serum concentration of vitamin D was measured.

Plasma 25(OH) vitamin D3 was assessed using enzyme-linked immunosorbent assay (ELISA) method and a kit of Immunodiagnostics Systems Ltd (IDS Ltd) by Auto Analyzer (Human Corporation, Germany). The sensitivity of the test was 5nmol/L and the intra and interassay coefficient of variations (CVs) were 3.37% and 3.891%, respectively. Calibration of the instruments was done as per the manufacturer's instructions and validation studies were done prior to the test. All measurements were done according to the standard operating procedures and samples were analyzed by a single technician using the same equipment throughout the study in a reference laboratory.

### The Second Phase

In the second phase of the study, to assess the effect of screening strategy on maternal and neonatal outcomes, Masjed-Soleyman participants were assigned to a screening program versus Shushtar participants acting as the nonscreening arm. Within the framework of the screening regimen, an 8-arm blind randomized clinical trial was undertaken to compare the effects of various treatment protocols. Due to the cost and complexity of the process, 800 pregnant women with vitamin D deficiency from Masjed-Soleyman were randomly allocated to 1 of the designed intervention programs according to the study Figure 1. The remaining women with vitamin D deficiency were referred to specialists for further treatments. Participants of Shushtar did not receive any vitamin D supplementation. However, the comparison of the basic confounders between the initial recruited sample in Masjed-Solayman and the women allocated to intervention indicated no statistically significant difference and hence no selection bias occurred during the allocation of treatment (Table 4).

### Sample Size Calculation

A cluster sampling method with PPS procedure was assigned. Sample size was calculated in screening group (Masjed-Soleyman) using the following formula (Figure 2) and assumption, resulting in 1537 subjects.

The same steps (except for ε=0.2) were used for calculation of sample size in no screening group (Shushtar), resulting in 900 subjects. Using the cluster sampling method, 1600 and 900 first trimester mothers were selected from among those receiving prenatal care in health centers in urban regions of Masjed-Soleyman and Shushtar, respectively.

Since the prevalence of the specified event is untreated or unrecognized and the number of people who have the risk factor (P) is high in the population, consequently, sample size needed for screening is considered sufficient. In other words, we define a correction coefficient by (1/P) for estimated sample size (n), and then we expect n (1/P) number of people to find the 0.15 difference with 5% significance level.

To compare different regimens used for vitamin D deficiency in the screening group, the sample size in each group was calculated based on the following formula (Figure 3) and assumption:

Considering loss to follow up of 10%, a total number of 100 in each study group was considered adequate.

**Figure 2 figure2:**
[figure not shown]
Sample estimation formula for the first phase of the study.

**Figure 3 figure3:**
[figure not shown]
Sample estimation formula for the second phase of the study.

### Randomization and Blinding

Subjects in each group of severe or moderate deficiencies were randomly divided into 4 subgroups using permuted block randomization by a biostatistician to achieve balance across treatment groups. The number of subjects per block was 8. Sealed opaque envelopes were assigned to each subject by a research assistant not associated in the trial. The dedicated study midwife treating the females, who did not participate in any subsequent phases of the study, was the only person who knew the group each patient belonged to (single blinded). Masking to treatment allocation was not possible and only those health care workers who determined pregnancy outcomes were blinded to treatment allocation.

### Intervention

The participants from Masjed-Soleyman entering the second phase of the study received vitamin D as follows.

#### Women With Severe Vitamin D Deficiency (Group A)

Group A1: Subjects were treated with 50,000 IU of oral vitD3 weekly for a total duration of 12 weeks.

Group A2: Subjects were treated with 50,000 IU of oral vitD3 weekly for a total duration of 12 weeks and then were on monthly maintenance dose of 50,000 IU vitD3 until delivery.

GroupA3: Subjects were treated with intramuscular administration of 300,000 IU vitD3; 2 doses for 6 weeks.

GroupA4: Subjects were treated with Intramuscular administration of 300,000 IU vitD3; 2 doses for 6 weeks and then were on monthly maintenance dose of 50,000 IU vitD3 until delivery.

